#### Interim analyses {21b}

There are no interim analyses planned.

#### Methods for additional analyses (e.g., subgroup analyses) {20b}

There are no subgroup analyses planned.

#### Methods in analysis to handle protocol non-adherence and any statistical methods to handle missing data {20c}

We will evaluate the loss of primary outcome data through intention-to-treat analysis. Missing data will be reduced to a minimum by using the multiple imputation.

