### Sample size calculation {14}

The sample size was calculated by G*power 3.1.9 according to the following conditions. According to Cohen’s criterion for effect size [38], 0.2, 0.5, and 0.8 are the boundary values for small, medium, and large effect sizes, respectively. According to Mecklenburg test results [39], 0.3 was selected to verify the small effect size, α was 0.05, the test power was 0.8, and the intraclass correlation coefficient was 0.6. The experiment will be performed with a two-way repeated measures analysis of variance, and the two groups will be measured four times. The final calculated sample size was 64. Considering a dropout rate of 25%, the actual required sample size should be 86.

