We will use IBM SPSS, version 26.0.1 for all statistical analyses, with 2-tailed tests as appropriate, and 2-sided *P* < 0.05 considered to be statistically significant. Baseline data on categorical variables (e.g., sex, occupation, education level) will be used to compare statistical differences between the trial and control groups using chi-square tests. For continuous variables (e.g., age, BMI, pain intensity, duration of knee pain), a normality test will be first conducted. If all groups meet normality, mean ± standard deviation (SD) will be used for statistical description, and two independent sample *T* tests or Mann–Whitney *U* tests will be used for comparison between groups. Otherwise, the median (interquartile spacing) will be used for statistical description, and a nonparametric test will be used for comparison between groups. If the results of the trial meet the conditions of homogeneity of variance and spherical symmetry, the two-factor four-level repeated measurement analysis of variance (group*time) is used; otherwise, the mixed effects model is used. According to the recommendations of the International Conference on Osteoarthropathy [42], the minimum clinically important difference (MCID) could be achieved when the pain intensity (primary outcome index: VAS) between the two groups is changed by 18 mm based on 100 mm. A chi-square test will be used to infer the proportion of the number of patients meeting the MCID between the two groups. The measurement results of all outcome indicators will calculate the effect size, and the size of the effect size between the two groups will be compared according to Cohen’s criteria [38] to draw the appropriate conclusions.

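### Choosing ANOVA or mixed model by a sphericity and variance check has no single answer under multiple imputation; name the mixed model in advance

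*Protocol article*

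**What the plan says.** Three statements in the protocol article bear on this point.

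- Statistical methods for primary and secondary outcomes {20a} makes intention-to-treat the main analysis set. It then makes the model depend on the trial's results: if homogeneity of variance and sphericity are met, "the two-factor four-level repeated measurement analysis of variance (group*time) is used; otherwise, the mixed effects model is used". The Abstract repeats the rule. The threshold is "2-sided *P* < 0.05 considered to be statistically significant".
- The section on non-adherence and missing data {20c} adds one sentence on method: "Missing data will be reduced to a minimum by using the multiple imputation".
- Sample size calculation {14} expects a material amount of missing data: "Considering a dropout rate of 25%, the actual required sample size should be 86".

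The article does not say on which dataset the two assumptions are checked, or what follows if imputed datasets disagree. Nor does it say that imputed datasets will be tested one by one or left uncombined.

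**The concern.** Each rule can be followed alone, but the two do not fit together. A classical repeated-measures ANOVA uses only patients with all four measurements. To keep every randomised patient in it when visits are missing, the gaps must first be imputed. Multiple imputation yields several completed datasets, each with its own sphericity and variance result. The rule in {20a} expects one verdict and receives several.

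The rule is also circular. The mixed-model branch can use the observed visits without imputation, so whether imputation is needed depends on the branch, while the branch may depend on imputed data. An analyst could check the assumptions in completers, in the first imputed set or by majority, and each choice is compatible with the text. The choice of primary model is then made after the data are seen, which a prespecified rule is meant to prevent.

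**Working it through.** **The plan's own figure.** The inputs from {14} are: "0.3 was selected to verify the small effect size"; "α was 0.05, the test power was 0.8, and the intraclass correlation coefficient was 0.6"; and a "two-way repeated measures analysis of variance, and the two groups will be measured four times". Reading 0.3 as Cohen's f, for the between-groups test:

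λ = f²·N·m / (1 + (m − 1)ρ) = 0.09 × 64 × 4 / (1 + 3 × 0.6) = 23.04 / 2.8 = 8.23, with 1 and 62 degrees of freedom.

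This gives power 0.806, and N = 64 is the smallest even total reaching 0.80. Then 64 / 0.75 = 85.3, rounded up to 86, or 43 per arm. The stated 64 and 86 reproduce, and nothing below disturbs them.

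**Can the imputed sets disagree, and what happens to the 5% level?** This was simulated with no treatment effect, testing group-by-time in 4,000 trials of 86 patients. The Monte Carlo standard error at 5% is √(0.05 × 0.95 / 4000), about 0.35 percentage points.

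- From the article: 43 per arm, four measurements, correlation 0.6, 25% dropout, two-sided 5%.
- Assumed: 20 imputations by sequential Bayesian regression; monotone dropout missing at random; compound symmetry with 0.6 or AR(1) with 0.75; sphericity judged by Mauchly's test at 5%; a Hotelling test standing in for the unstructured mixed model when sphericity was rejected. The variance-homogeneity check was not simulated. Dropout of 10% was run as a second case.

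Two standard pooled tests were used, with k = 3 degrees of freedom and M imputations:

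- Pooled Wald (D1): r = (1 + 1/M)·tr(BU⁻¹)/k and D1 = q̄ᵀU⁻¹q̄ / [k(1 + r)], where q̄ is the mean contrast vector, U the mean within-imputation covariance and B the between-imputation covariance.
- Pooled test statistics (D2): with w = 3F in each set, r₂ = (1 + 1/M)·var(√w) and D2 = [w̄/k − r₂(M + 1)/(M − 1)] / (1 + r₂).

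Results are compound symmetry / AR(1):

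| Quantity | 25% dropout | 10% dropout |
|---|---|---|
| Sphericity verdict differs between sets | 63% / 1% | 27% / 0.2% |
| Significance verdict differs between sets | 43% / 40% | 18% / 15% |
| False positives, pooled D1 | 5.1% / 5.1% | 5.4% / 5.0% |
| False positives, pooled D2 | 4.6% / 5.2% | 5.0% / 5.3% |
| False positives, median P | 10.9% / 11.4% | 7.0% / 6.4% |
| False positives, averaged F on the ordinary table | 11.8% / 12.5% | 7.0% / 7.4% |
| False positives, one imputed set | 14.5% / 15.0% | 8.0% / 7.2% |
| False positives, all sets significant | 1.8% / 1.7% | 1.8% / 1.7% |

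As a check, ANOVA on the full data before deletion, in the 25% runs, rejected in 5.1% under compound symmetry and in 6.6% under AR(1), where sphericity fails.

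Under compound symmetry sphericity is true and Mauchly's test rejects by chance, so the sets often split; in 29% of trials at 25% dropout the split was at least 20/80. AR(1) violates sphericity, and the sets almost always agree. D1 and D2 each apply one fixed test to every set. They therefore settle how to combine results, but not which model to combine when the verdicts differ.

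**The case against.** A reader might infer that the plan does not deliver its 5% error rate. The documents do not support that. Combining results is part of multiple imputation, and the article nowhere plans to read off one set, a median P or an averaged F. With the article's sample size and dropout, the pooled tests hold the level. The inflated rows describe misuse, and another unpooled rule, requiring every set to be significant, is conservative. The wording in {20c} speaks of reducing missing data, which may suggest gap-filling, but that is not a plan to skip pooling. The number of imputations and the pooling formula are details that an article may leave to the analysis plan; their absence is no finding.

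The size of the disagreement also depends on assumptions. The 63% belongs to exact compound symmetry and falls to 1% under AR(1). The 25% is a sample-size allowance; section {18b} says that outcomes will be collected from participants who stop or depart from the intervention, so fewer visits may be missing. The mixed-model branch does not need imputation, and the per-protocol analysis uses completers.

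All of this stands, and it removes the error-rate claim. It does not say which model governs when imputed sets disagree. An analysis plan could settle that only by supplementing or replacing the published rule.

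**Conclusion.** The point holds as a misfit between two stated rules. The data-driven choice in {20a} presupposes one verdict, and under the multiple imputation in {20c} there may be several. How often this happens is uncertain: about 63% of simulated trials under compound symmetry and about 1% under AR(1) at 25% dropout, and 27% and 0.2% at 10%. The real covariance of the VAS is not known from the article, and the variance check was not modelled.

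The point does not establish a loss of the 5% level. Properly pooled tests gave 4.6–5.2% at 25% dropout. The rise to about 11–15% is conditional on unpooled or naively averaged use, and is smaller at 10% dropout (6.4–8.0%). This is a free improvement to the plan, not a threat to the trial's validity.

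**What to change.** In the Abstract and in {20a}, remove the sphericity and variance condition. Name one primary VAS analysis in advance: a mixed model for repeated measures, fitted by REML with unstructured covariance to all observed visits. Report the group difference at week 12, the time point on which Outcome measures {12} says the trial focuses. In {20c}, state that this analysis uses the observed visits without imputation. If multiple imputation is kept, use it as a sensitivity analysis of the same week-12 contrast, pooled by Rubin's rules.

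The cost is wording only: the mixed model is already the plan's fallback, and enrolment stays at 86. Two limits should be stated. A random-intercept mixed model on the observed data rejected in 5.3% of null trials generated under compound symmetry; the unstructured version recommended here was not itself simulated. The calculation in {14} reproduces as a between-groups test over the four measurements, and power for the week-12 contrast was not checked here.

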#### Data monitoring {21a}

A Data & Safety Monitoring Committee is not necessary in this research since the interventions are low-risk and significant adverse events (incapacitating, life-threatening, hospitalization, or death) are incredibly improbable.

#### Composition of the coordinating center and trial steering committee {5d}

A group of individuals oversees this trial, including a principal investigator who is in charge of both the prosecution and medical treatment of the participants, two data managers who ensure data capture and quality, a study coordinator who manages registration and study visits, and a study physician who selects potential participants and oversees proper follow-up. Every Monday, the team meets; however, neither the trial steering committee nor a stakeholder/public involvement group are present.

#### Auditing {23}

Twice a month, independent supervisors make on-site visits to examine the existence and accuracy of the investigation files. Additionally, the monitoring team will check the following statistics on 20% of the patients who are chosen at random: Source data, inclusion and exclusion criteria, missing scales, reporting, and informed consent.

#### Ethics {24}

The study will be conducted in accordance with the provisions of the Declaration of Helsinki and has been approved by the Biomedical Ethics Committee of West China Hospital, Sichuan University, and is registered with the Chinese Clinical Trial Center.

#### Provisions for post-trial care {30}

Should any risks arise during the treatment phase, any adverse events attributed to the study will be managed by the project team at no cost to the participant. In the case of serious adverse events deemed to be associated with the clinical trial, the project team will provide the necessary treatment free of charge. For any financial losses incurred, the research group will offer corresponding monetary compensation, including a 300 yuan subsidy for transportation and accommodation, provided that the participant can furnish legally valid proof of loss.

#### Dissemination plans {31a}

The results will be reported in peer-reviewed journals, national and international conferences, and various media to share the findings with patients, clinicians, and the public.

#### Protocol amendments {25}

Significant alterations to the protocol will be submitted to the Biomedical Ethics Committee of West China Hospital, Sichuan University for approval. Patients engaged in the study are required to sign informed consent prior to their participation. In the event of any updates to the study protocol, patients will be requested to sign the updated informed consent form. Following this, notifications regarding the updated protocol will be disseminated to the researchers, General Practitioners, and the patients via email.

#### Confidentiality {27}

Research data will be marked with a special participant identification code throughout the trial. The study team will be the only ones with access to the key to this identification code list. The lead investigator will adhere to research protocols to record and secure the key after the study is finished. No information identifying a patient will be disclosed in publications.

## Discussion

Despite the proven benefits of multicomponent exercise therapy for knee osteoarthritis (KOA) in high-quality randomized controlled trials [43, 44], its implementation as a core treatment approach remains underutilized. Challenges such as limited outpatient treatment time and inadequate medical resources hinder the promotion of this model through traditional in-person doctor-patient communication in clinical practice. In response, the development of telemedicine-guided (TG) therapy offers an innovative solution for managing KOA patients. Previous studies have demonstrated that telemedicine interventions for KOA can be as effective as standard care [45, 46]. By leveraging telemedicine, there is an opportunity to establish a sustainable healthcare system that addresses the challenges associated with delivering optimal care for KOA patients.

The primary objective of this trial is to assess the reliability and sustainability of telemedicine-supported multicomponent exercise therapy in the management of knee osteoarthritis (KOA) patients. By investigating the effectiveness and feasibility of this approach, the trial holds the potential to enhance the accessibility and quality of care provided to individuals with KOA. The findings from this study could contribute valuable knowledge and insights to optimize the management of KOA and improve patient outcomes. Our trial incorporates the use of wearable devices to monitor exercise compliance, which is a notable strength. Adherence to exercise is a critical factor influencing clinical efficacy, particularly in the context of knee osteoarthritis (KOA) where patients lack direct supervision from doctors or physical therapists in home settings, unlike in outpatient settings. Thus, coaching and monitoring exercises become crucial elements when implementing telemedicine for managing KOA at home. However, there are certain limitations to consider. Firstly, it is not feasible to blind patients and physical therapists in our trial. Secondly, the trial requires the use of smartphones, which may pose a limitation in terms of accessibility for certain individuals. Lastly, while wearable devices provide valuable insights into exercise occurrence, they are unable to fully assess exercise accuracy. This limitation is inherent to the current technological capabilities and remains unresolved at present.

### Trial status

Recruitment will be started in July 2023, and it is estimated to have a total duration of 12 months. This protocol is version number 12 dated October 14, 2023.

## Abbreviations

KOA: Knee osteoarthritis
RCTs: Randomized controlled trials
TG: Trial group
CG: Control group
IMUs: Inertial Measurement Units
VAS: Visual analog scale
WOMAC: Western Ontario and McMaster Universities Osteoarthritis Index,
TUG: Time up go test
SF-36: MOS Item Short-Form Health Survey
PSEQ: Pain Self-Efficacy Questionnaire
DASS21: Depression-Anxiety-Stress Scale
TSK: Tampa Scale of Kinesiophobia
PCS: Pain Catastrophizing Scale
EARS: Exercise Adherence Rating Scale
SPIRIT: Standard Protocol Items: Recommendations for Interventional Trials
COA: Chinese Orthopedic Association
BMI: Body mass index
ITT: Intention-to-treat
PP: Per-protocol
SD: Standard deviation
MCID: Minimum clinically important difference
